### Data management {19}

Once the data is gathered and the study is completed, the raw materials will be kept in a locked file cabinet in the office of the Researcher. Electronic data will be kept secure and password protected. Only the Researcher will have access to the data. All materials will be shredded and discarded 5 years after completion of this study.

### Confidentiality {27}

Data obtained in this study will be kept and handled confidentially, in accordance with applicable laws and/or regulations. The participant will remain anonymous in any report of this data.

### Plans for collection, laboratory evaluation and storage of biological specimens for genetic or molecular analysis in this trial/future use {33}

Not applicable as no biological specimens will be collected for this study.

## Statistical methods

### Statistical methods for primary and secondary outcomes {20a}

All data will be analyzed using the IBM Statistical Product and Service Solutions (IBM SPSS). Descriptive analysis for categorical data such as gender, marital status, hand dominance, type of wrist fracture, and educational level will be expressed in frequency, percentage, and proportion. Descriptive statistics will be used to analyze continuous data including age, Quick-DASH score, PRWE score, IES-R score, PPT score, AROM of the forearm and wrist, TAM for the digits, and grip strength. These results will be expressed as mean, standard deviation, minimum and maximum if the data is normally distributed or as median and interquartile range. If the data is not normally distributed, sub-analysis will be conducted to determine the outlier and the outlier will be extracted from the data set if it shows significant influence. A mixed model ANOVA will be used to test the primary outcome of this study by evaluating the mean difference between and within groups of the Quick-DASH scores obtained at baseline and after the 12th therapy session. The difference in the initial and final PRWE score, IES-R score, PPT score, AROM of the forearm and wrist, and TAM of the digits and grip strength will be analyzed using a mixed model ANOVA. Depending on the results of the aforementioned analyses, other sub-analysis will be performed as necessary.

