#### Sample size {14}

In regard to the primary outcome of this study, the sample size required was calculated with a G* power sample size calculator. Analysis was done using ANOVA repeated measures, within-between interaction in *F* tests family. A priori type of power analysis was used to compute the required sample size. Analysis was done with Cohen-f effect size at 0.25 for a medium effect, alpha error at 0.05, and 80% power. There are two groups (Control and Intervention) with two sets of measurements (initial baseline and final) to be compared. Correlation among repeated measure was set at 0.5 and the non-sphericity correction was 1.0. The result of priori analysis indicates a total of 34 participants will be needed; however, a 10% dropout rate (4 participants) is anticipated bringing the total sample size required to 38 participants.

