## Assignment of intervention: blinding

### Who will be blinded {17a}

Therapist A and Therapist B will be blinded to the participant’s group allocation. The Researcher will not be blinded as the Researcher will be involved in the craft-making sessions. Similarly, the participants once assigned to a group will no longer be blinded to the other group’s intervention. To ensure that Therapist A and Therapist B remain blinded over the 6-week study, the Researcher will continually remind each participant not to reveal his/her group allocation to Therapist A or B.

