### Methods in analysis to handle protocol non-adherence and any statistical methods to handle missing data {20c}

Missing data will be replaced with the mean imputation method. Intention-to-treat analysis will be used for participants that are non-adherent.

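### Influential values are removed when data are non-normal, with no requirement that they be errors and no analysis that keeps every value

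*Protocol article*

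**What the plan says.** Under Statistical methods {20a}, after the descriptive summaries, the protocol article states: "If the data is not normally distributed, sub-analysis will be conducted to determine the outlier", and then that "the outlier will be extracted from the data set if it shows significant influence". The next sentence begins "A mixed model ANOVA will be used to test the primary outcome of this study", and the same model follows for every secondary outcome.

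Three other sections bear on this. Section {20c} says "Intention-to-treat analysis will be used for participants that are non-adherent", and that missing values are filled by mean imputation. Section {17a} says "The Researcher will not be blinded as the Researcher will be involved in the craft-making sessions". Section {19} says "Only the Researcher will have access to the data".

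**The concern.** The rule has two conditions: the data look non-normal, and the value matters to the result. Neither shows that the value is wrong. A patient who recovered very well or very badly is a genuine randomised outcome, and such patients weigh heavily in a comparison of about 17 per arm.

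Deletion after inspection does two kinds of harm. It can move the estimated group difference, in either direction. It also shortens the tails from which the error variance is estimated, while the test treats the remaining values as a complete sample, so p-values can be too small and confidence intervals too narrow.

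The choice of outlier definition, influence measure, data level (raw or change score) and pooling (by arm or overall) is left open, so it could follow the data. Nor does {20c} say whether an extracted value is then treated as missing and mean-imputed.

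**Working it through.** **Inputs from the protocol article.** Sample size {14}: "Cohen-f effect size at 0.25 for a medium effect, alpha error at 0.05, and 80% power"; "Correlation among repeated measure was set at 0.5 and the non-sphericity correction was 1.0"; two groups, two measurements, 34 evaluable participants, 38 after 10% dropout.

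**Inputs assumed, because the document gives none.** Equal arms (17 per arm), a Shapiro-Wilk gate at p < 0.05, the outlier rules, and the distributions.

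**1. Reproduce the plan's figure.** For the within-between interaction, λ = f²·N·m/(1 − ρ), with df 1 and N − 2.
- N = 32: λ = 0.0625 × 32 × 2/0.5 = 8.0, power 0.781.
- N = 34: λ = 0.0625 × 34 × 2/0.5 = 8.5, power 0.807.
- Dropout: 34/0.9 = 37.8, rounded up to 38.

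The stated 34 and 38 are reproduced. The document's only error rate is the nominal 5%. It states none for the outlier rule.

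**2. The test.** With two groups and two times, the interaction F equals the square of the two-sample t on change scores. Type I error is the share of simulated null trials with p < 0.05 after the rule is applied.

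**3. Simulation error.** There were 4,000 to 5,000 trials per scenario. At a true 5%, the standard error is √(0.05 × 0.95/5000) = 0.31 percentage points, or 0.34 with 4,000. Differences of a few tenths mean nothing.

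**4. Type I error (%), 17 per arm, after the gate, by distribution of the change score:**

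| Assumed rule | t, 4 df | gamma, shape 2 | lognormal | exponential |
|---|---|---|---|---|
| All within-arm 1.5 IQR outliers removed | 7.3 | 10.7 | 16.9 | 14.8 |
| Same, only if Cook's D > 4/n | 6.6 | 8.1 | 8.6 | 9.0 |
| Only the single most influential outlier removed | 5.8 | 6.6 | 6.0 | 6.6 |

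Requiring Cook's D > 1 gave the same results as keeping all data (4.2–5.0). Other runs of the first row gave 6.6–7.0, 10.6–10.8, 13.7–16.7 and 14.9–15.6. The lognormal spread exceeds simulation error, so that cell is indicative only.

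**5. Other rules, over a range of distributions.**
- Pooled boxplot: 4.5–6.3%.
- |z| > 3: 4.9–5.7%.
- Residual beyond 2 SD: 5.2–8.0%.
- Cook's D > 4/n alone: 5.2–7.5%.
- Within-arm boxplot repeated until no outliers remain: up to 22%.
- Deletion only when it yields significance: up to 15–17% for strongly skewed data.

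**6. Near-normal and bounded scores.** Normal data with the within-arm boxplot gave 5.3–5.8%. A bounded Quick-DASH model (baseline mean 60, final mean 30, clipped at 0 and 100) gave 5.8%, and the gate fired in 5.5% of trials. A second bounded model, with raw scores checked at both times, gave 6.9–7.4%, and the gate fired in 65–71% of trials. In that second model the rule removed 1.2 participants per trial on average at 17 per arm. With a skewed final score it removed 3.3, and with both scores skewed 4.3. The last two are close to the whole dropout allowance of 4.

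**7. With the rule removed.** Keeping all values gave 3.8–5.5% in every scenario.

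**The case against.** **The damage may be small.** This largely stands. Several common rules leave the error rate near 5–6%, and a strict influence cut-off may delete nothing. A reader might infer that the plan itself implies a rate of 7–16%. The document does not support that: those figures need within-arm boxplot deletion of heavy-tailed or skewed changes, and they ignore the condition that the value be influential. Nor does a bounded scale show that the trigger will often fire for Quick-DASH. The protocol reports no skew, and the simulated firing rate ran from 5.5% to 71% with the model and with what was checked.

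**The criteria may be in an analysis plan not shown.** That is fair for cut-offs, and their absence is not the main point. The protocol commits to removing valid values, and a cut-off would not cure that.

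**The sentence may govern only the descriptive summaries that precede it.** This is possible from its position. But it speaks of removal from the data set, and the ANOVA sentence follows with no statement that the values return.

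**It does not contradict intention-to-treat.** Correct. Section {20c} words that principle for non-adherent participants, so the conflict is one of principle and not of text.

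**Nobody is named as the person who decides on outliers.** Also correct. A reader might infer that the unblinded Researcher decides. Sections {17a} and {19} establish only that the Researcher is unblinded and alone has data access, which makes the inference natural but not stated.

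**Illustrations of bias are invented.** If 3 of 17 in one arm are assumed to be shifted by 4 SD, deletion cuts the estimated effect from 0.70 to 0.36 SD. This shows that a real effect can be hidden. It does not predict the size in this trial.

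**Conclusion.** The rule is wrong as written. It reaches the primary analysis, is triggered by the outcome data, does not require an error, and leaves no described analysis of all values.

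Its effect on the false-positive rate is a range that rests on assumptions: about 5–6% for near-normal changes or mild rules; about 6–9% for heavy-tailed or skewed changes when outliers must also exceed Cook's D of 4/n; and over 15% for unrestricted within-arm boxplot deletion of strongly skewed changes. The comparison is about 4–5.5% with all data kept. All figures assume 17 per arm and a Shapiro-Wilk gate. No single value in the range should be quoted as a property of this plan. The width of the range is itself an argument against the rule, because the text as it stands permits each of these choices.

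**What to change.** Delete the extraction sentence from {20a} and state instead:
- All valid observed values of randomised participants stay in the planned mixed ANOVA for the primary and secondary outcomes.
- Only verified recording errors are corrected, against the source record and without reference to group.
- Any analysis that excludes outliers is labelled a sensitivity analysis and is reported beside the full one, with its criterion given.
- If residuals are clearly non-normal, a permutation or bootstrap test of the same group-by-time effect may be reported alongside. This is optional, since the full-data analysis already held close to 5% in the simulations.

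No change of model is needed. The cost is a few sentences and slightly more analysis work. The trial status section reports that data collection is still under way, so the change can be made and dated before analysis.

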**Methods:**

Priori analysis determined that 38 patients will be needed for this superiority randomized controlled trial to be conducted in a hand and upper limb rehabilitation center. Eligible participants must comprehend English, be diagnosed with lower-third forearm fracture(s) stabilized by open reduction internal fixation, and referred to therapy within 2–4 weeks of surgery. Following the CONSORT guidelines, participants will be randomly assigned to a Control (conventional therapy) group or an Intervention (conventional therapy and craft) group. Twice weekly for 6 weeks, Therapist A will provide both groups with 1-h of conventional therapy while the Intervention group will also receive 15 min of craft-making supervised by the Researcher. The primary outcome of disability will be measured with the Quick-Disabilities of Arm, Shoulder and Hand. The secondary outcome measurements include the Patient-Rated-Wrist-Evaluation; Impact of Event Scale-revised and physical performance, i.e., the Purdue Pegboard Test, AROM, and grip strength. All outcome measures will be obtained by Therapist B prior to the 1st therapy visit and after the 12th visit. Descriptive analysis will be done for the categorical and continuous data and a mixed model ANOVA for analysis of the initial and final assessment scores within and between groups.

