#### Outcomes {12}

The primary outcome implemented in this study is the Quick-DASH (Disabilities of the Arm, Shoulder and Hand) to assess upper limb disability. The secondary outcomes include the Patient Rated Wrist Evaluation (PRWE), which is specific for evaluating wrist disability and the Impact of Event Scale-Revised (IES-R) for rating post-traumatic stress. Additional secondary outcomes include components of physical performance (measured by)—dexterity (Purdue Pegboard Test), AROM of forearm, wrist and fingers (goniometer), and grip strength (Jamar™ dynamometer).

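### The planned mixed ANOVA is valid and powered as stated, but adjusting the final Quick-DASH for its baseline by ANCOVA would raise power from about 81% to 90% on the protocol's own planning inputs

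*Protocol article*

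**What the plan says.** The Outcomes section (item 12) fixes the endpoint: "The primary outcome implemented in this study is the Quick-DASH (Disabilities of the Arm, Shoulder and Hand) to assess upper limb disability". The statistical methods section (item 20a) gives the test: "A mixed model ANOVA will be used to test the primary outcome of this study by evaluating the mean difference between and within groups". Two scores per participant enter this test, one from before treatment and one from the end of the 12 sessions. The abstract describes it in similar terms: "a mixed model ANOVA for analysis of the initial and final assessment scores within and between groups". The secondary outcomes are also to be analysed by mixed ANOVA.

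The Sample size section (item 14) is more specific about the effect: "Analysis was done using ANOVA repeated measures, within-between interaction". It assumes a Cohen's f of 0.25, a 5% alpha and 80% power, for two arms each measured twice. On the dependence between the two visits it states: "Correlation among repeated measure was set at 0.5 and the non-sphericity correction was 1.0". This leads to 34 participants, raised to 38 for 10% dropout.

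The Objectives section (item 7) states only between-arm hypotheses. None of these sections adjusts the final score for baseline.

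**The concern.** A baseline Quick-DASH is collected from every participant, so its cost is already paid. How much precision it returns depends on the model. A change score subtracts the whole baseline, as if each point at baseline carried forward as one point at the end. ANCOVA estimates how much carries forward. When the correlation between visits is moderate, subtracting the whole baseline adds noise. With about 17 participants per arm, the difference can decide whether a real effect is detected.

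There is also a smaller matter of wording. A mixed ANOVA with two groups and two visits yields three tests: group, time, and group by time. The abstract and item 20a speak of differences between and within groups without saying which test decides. The Sample size section does name it, and the analysis text should carry that over.

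**Working it through.** **Inputs from the Sample size section.** f = 0.25, alpha = 0.05, power 80%, two groups, m = 2 measurements, correlation rho = 0.5, non-sphericity correction 1.0, N = 34 evaluable.

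**Inputs assumed here.** 17 per arm (the protocol fixes no allocation ratio) and the same variance at both visits. Effects are in units of the SD at one visit, because the protocol gives no Quick-DASH SD in points.

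**1. Reproduce the stated sample size.** For the within-between interaction the noncentrality is

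lambda = f² × N × m / (1 − rho) = 0.0625 × 34 × 2 / 0.5 = 8.5, with df (1, 32).

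Power is 80.7% at N = 34 and 78.1% at N = 32, so 34 is the smallest even number reaching 80%. Allowing 10% dropout gives 38. The stated figures are correct.

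**2. Translate the effect.** With two visits the interaction is the t-test on change, for which lambda = (N/4) × D² / [2(1 − rho)], where D is the difference in mean change. Equating this with step 1 gives D = 4f = 1.0 SD.

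**3. Compare error variances.** In units of the single-visit variance:

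- change score: 2(1 − rho) = 2 × 0.5 = 1.00
- ANCOVA: 1 − rho² = 1 − 0.25 = 0.75

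The ratio is (1 + rho)/2 = 0.75, a 25% reduction. The ratio is below 1 for any rho below 1. At rho = 0.5 the change-score variance equals that of the final score alone, so subtracting the baseline gains nothing over ignoring it.

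**4. Power for ANCOVA.** lambda = (N/4) × D² / (1 − rho²) = 8.5 / 0.75 = 11.33, with df (1, 31). Power is 90.3%. A simulation of 20,000 trials gave 89.7% for ANCOVA and 80.9% for the interaction.

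**5. Sensitivity to the correlation** (D = 1.0 SD, N = 34):

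| rho | Interaction | ANCOVA | Gain (points) |
|---|---|---|---|
| 0.3 | 66.6% | 84.1% | 17.5 |
| 0.4 | 73.3% | 86.9% | 13.6 |
| 0.5 | 80.7% | 90.3% | 9.6 |
| 0.6 | 88.5% | 94.2% | 5.7 |
| 0.7 | 95.4% | 97.7% | 2.3 |

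**6. The same gain in other terms, at rho = 0.5.** If all 38 are evaluable, power is 85.1% against 93.3%. The smallest effect detectable with 80% power at N = 34 falls from 0.99 to 0.86 SD. ANCOVA reaches 80% power for D = 1.0 with 26 participants instead of 34.

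**7. Why the deciding term should be named.** The group main effect averages each participant's two scores. This halves the craft effect to 0.5 SD, with variance (1 + rho)/2 = 0.75, so lambda = 8.5 × 0.25 / 0.75 = 2.83 and power is 37.2%. The time main effect reflects improvement common to both arms. If, as an illustration, both arms improved by 0.5 SD with no craft effect at all, it would be significant in 80.7% of trials.

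**The case against.** The strongest reply is that nothing here is an error. The interaction is an unbiased test of the randomised comparison, the trial is sized on exactly that test, and the sample size is right for it. That stands in full. A reader might infer from the comparison with ANCOVA that the planned test is invalid or the trial underpowered; step 1 shows that it is neither.

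A second reply is that the intended term can be recovered. The Sample size section names the interaction for the primary outcome, and the Objectives section states only comparisons with conventional therapy alone. This also stands. A reader might infer from the between-and-within wording that improvement inside the craft arm would count as evidence for craft. No section says so. Nor does the protocol give recovery figures from which to predict that the time effect will be significant; the 0.5 SD in step 7 is only an illustration. And the group main effect does contain the craft effect, in diluted form, so it would be wrong to say that it does not test craft.

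A third reply is that the gain is conditional. The correlation of 0.5 is a planning assumption, and at 0.7 the gain is about 2 points. That is correct and limits the size of the claim. It does not reverse it, since ANCOVA has the higher power at every correlation in the table.

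Finally, replacing a published primary method while the trial is running is more than an edit of wording. That is accepted, and it is counted under the cost.

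**Conclusion.** The point holds as an efficiency gain, not as the correction of an error. On the protocol's planning inputs, ANCOVA raises power by about 10 percentage points at N = 34. The gain is about 17 points at a correlation of 0.3 and about 2 points at 0.7. These figures rest on a 1.0-SD effect, equal variances at the two visits and 17 per arm. The envelope draw does not guarantee equal arms; unequal arms would lower both powers slightly and leave their order unchanged. The unnamed deciding contrast is a minor matter of clarity, because the Sample size section already shows the intent.

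**What to change.** By a documented amendment made before outcome data are examined:

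1. Make the primary analysis an ANCOVA of final Quick-DASH on group, with baseline Quick-DASH as covariate. Report the adjusted between-group difference with its 95% confidence interval.
2. Use the same model for each secondary outcome, with that outcome's own baseline as covariate.
3. In the abstract and item 20a, name the single between-arm contrast that decides the trial, and state that within-group changes are descriptive. If the mixed ANOVA is kept, this clarification is still worth making: the contrast is then the group-by-time interaction, as in the Sample size section.

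The sample size can stay at 34 evaluable and 38 recruited, with the gain taken as extra power. No new data, visits or participants are needed. The cost is one degree of freedom and an amendment to the published analysis method. The Trial status section reports that data collection was still under way under a single protocol version, so the amendment should record its date and confirm that outcome data had not been examined.

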### Interim analyses {21b}

There are no interim analyses or stopping guidelines for this study.

### Methods for additional analyses (e.g., subgroup analyses) {20b}

There are no additional analyses planned for this study.

### Methods in analysis to handle protocol non-adherence and any statistical methods to handle missing data {20c}

Missing data will be replaced with the mean imputation method. Intention-to-treat analysis will be used for participants that are non-adherent.

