### Plans to promote participant retention and complete follow-up {18b}

There are no plans to promote participant retention or to complete follow-up. Follow-up data will not be collected for participants who discontinue or deviate from intervention protocols.

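### Single mean imputation of uncollected final scores shrinks the primary effect or understates its standard error, even if dropout is completely random

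*Protocol article*

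**What the plan says.** Three statements in the protocol article act together.

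- The section on non-adherence and missing data {20c} fixes the method: "Missing data will be replaced with the mean imputation method". It names neither the mean to be used nor a sensitivity analysis. It continues: "Intention-to-treat analysis will be used for participants that are non-adherent".
- The section on retention and follow-up {18b} states: "Follow-up data will not be collected for participants who discontinue or deviate from intervention protocols".
- The sample size section {14} expects the loss: "a 10% dropout rate (4 participants) is anticipated bringing the total sample size required to 38 participants". The base figure is that "The result of priori analysis indicates a total of 34 participants will be needed".

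The primary analysis, under Statistical methods {20a}, is a mixed model ANOVA of baseline and final Quick-DASH scores.

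**The concern.** Participants who stop or deviate have no final score but stay in the intention-to-treat analysis, so their primary outcome is filled in with a mean and analysed as if observed. Both readings of the rule fail.

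- **Overall mean.** Each filled-in final score has the same expected value in both arms. Those participants carry no treatment effect and pull the estimate toward zero.
- **Arm mean.** The filled-in scores add no information about the effect, but the ANOVA counts 38 participants instead of 34. The standard error is then too small and the degrees of freedom too many.

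Neither failure needs informative dropout. What is at stake is the primary estimate and its interval in a small trial with power only just above 80%. The 4 extra participants were recruited to protect 34 evaluable ones; filling in their scores does not restore what was lost.

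**Working it through.** **Inputs from Sample size {14}.**

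- Effect size, error rate and power: f = 0.25, α = 0.05, power 80%.
- Design: two arms, each measured twice, so m = 2.
- Correlation between the two scores, taken from this statement: "Correlation among repeated measure was set at 0.5 and the non-sphericity correction was 1.0".

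**Assumptions.** 19 participants per arm (the plan fixes no allocation ratio); missing final scores split evenly between arms; missing completely at random. Scores are in units of the between-participant SD. With two groups and two time points, the interaction test is a t-test on change.

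**Step 1: reproduce the plan's figure.** The noncentrality is λ = f² × N × m / (1 − ρ), on 1 and N − 2 degrees of freedom.

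- N = 32: λ = 0.0625 × 32 × 2 / 0.5 = 8.0, power 0.781.
- N = 34: λ = 0.0625 × 34 × 2 / 0.5 = 8.5, power 0.807.

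So 34 reproduces. Inflating for dropout, 34 / 0.9 = 37.8, giving 38.

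**Step 2: the effect implied by f = 0.25.** The variance of change is 2(1 − ρ) = 1. For the t-test on change, λ = δ² × N / 4. Setting δ² × 34 / 4 = 8.5 gives δ = 1.0 SD.

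**Step 3: overall mean, 4 missing (2 per arm).** Only 17 of 19 participants per arm carry the effect, so the expected estimate is 1.0 × 17/19 = 0.895 SD.

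**Step 4: arm mean, 4 missing.** The estimate is unbiased.

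- True variance of an arm's mean change (mean of 17 finals minus mean of 19 baselines): 1/17 + 1/19 − 2ρ/19 = 1/17 at ρ = 0.5. The true SE of the difference is √(2/17) = 0.343.
- Variance that the ANOVA sees within an arm: expected sum of squares 16 (finals) + 18 (baselines) − 2 × 0.5 × 16 (covariance) = 18, on 18 degrees of freedom, so 1.0. The model SE is √(2/19) = 0.324.
- Ratio: 0.324 / 0.343 = 0.946. The model SE is 5 to 6% too small; averaged over simulated trials it is 0.322 against 0.342, a ratio of 0.94.

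**Step 5: simulation of the planned test (40,000 to 60,000 trials per scenario).**

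| Missing of 38 | Method | Effect (SD) | Type I error | Power |
|---|---|---|---|---|
| 4 (planned) | Observed cases only | 1.00 | 5.0% | 81% |
| 4 (planned) | Overall mean | 0.89 | 5.0% | 76% |
| 4 (planned) | Arm mean | 1.00 | 6.3% | not comparable |
| 8 (assumed) | Observed cases only | 1.00 | 5% | 75% |
| 8 (assumed) | Overall mean | 0.79 | 5% | 64% |
| 8 (assumed) | Arm mean | 1.00 | 8% | not comparable |

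Arm-mean power is not comparable because the test exceeds its nominal level. The 8-missing rows are an assumption: 8/38 = 21%, twice the planned rate. There, the expected overall-mean effect is 1 − 8/38 = 0.789 SD.

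At ρ = 0.3 and 0.7 with 4 missing, the overall mean again gives 0.89 SD and the arm mean a type I error of about 6.3%.

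**The case against.** **The damage at the planned rate is small.** This stands. About 10% attenuation and 5 points of power, or a type I error of 6.3% instead of 5%, is a modest fault.

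**The significance test is not invalid under every reading.** This also stands. A reader might infer that the primary p-value is wrong whichever mean is used. Under the overall mean the null test keeps its 5% level, and with 4 missing the 95% interval covers the design effect about 94% of the time. The harm there is attenuation and lost power.

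**Observed-data analysis is not always better.** A reader might infer a general ranking. The comparison above holds under random missingness. If dropout depends on the unseen recovery, an analysis of observed scores is biased too, and the follow-up rule in {18b} makes such dropout plausible. That is a reason for a sensitivity analysis and for collecting the scores, not a defence of mean imputation.

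**A power loss from 81% to 64% would be overstated.** The 64% belongs to 8 missing, where the observed cases themselves give about 75%. The loss due to imputation is then about 11 points.

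**The rule may concern only scattered questionnaire items.** This is weak. The Quick-DASH formula already averages over the items answered, and the next sentence of {20c} promises intention to treat for participants whose final scores {18b} says will not be collected.

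**A separate analysis plan may exist.** The protocol states a definite method and nothing else in it corrects that method, so this is not a matter of detail left out.

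**Conclusion.** The concern holds, as a should-fix. The stated rule gives either a biased primary estimate or an understated standard error even in the most favourable case, data missing completely at random. Which fault occurs depends on a choice that the protocol leaves open.

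The size at the planned dropout is set out in the working. It rests on 19 per arm, an even split of missing scores, ρ = 0.5 from the plan, and imputation of the final score rather than the change score. If change scores were imputed with the arm mean, the standard error would be about 11% too small and type I error about 8%. The damage grows with the missing share, and participants who deviate could add to the 4 expected dropouts.

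The documents do not show that the trial's conclusion would be reversed, nor that observed-data analysis is safe under informative dropout.

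**What to change.** Replace the imputation sentence in {20c} with wording such as:

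> No single mean imputation. The primary analysis uses all observed baseline and final Quick-DASH scores in a likelihood-based mixed model for repeated measures (SPSS MIXED), testing the group-by-time interaction. As a sensitivity analysis, missing final scores are multiply imputed by arm using baseline score, and the imputed values are shifted by up to 12.85 points in each arm.

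The 12.85 points are the minimal clinically important difference that the protocol gives for the Quick-DASH. The shifts address dropout that depends on the unseen outcome. The test of the group-by-time interaction stays as planned.

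Also reconcile the intention-to-treat statement in {20c} with {18b}, by seeking the already planned final assessment from participants who stop or deviate. No analysis method recovers scores that were never collected.

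The cost is a change of wording, slightly more analysis in the package already named, and effort to reach participants who have left. If scores remain missing at the planned rate, precision will reflect about 34 participants rather than 38, which is the number on which the trial was powered.
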